## Aim and hypothesis

### Primary exploratory aim: auditory-driven changes in body perception

The primary aim of this study is to gain an exploratory understanding of the influence on body perception of non-naturalistic auditory information in participants with subthreshold EDs symptomatology using two body illusions. The scarce literature on the topic precludes us from considering a confirmatory model. As a result, the following hypotheses are all descriptive–exploratory.

**Hypotheses 1 (H1)**: Participants with subthreshold ED symptomatology will differ from participants without ED symptomatology in their degree of body image distortion. This hypothesis is exploratory, as alternatively, both groups may show the same degree of distortion.

H1 is based on previous literature that has shown a conflicting set of results. While there is strong evidence to suggest that young females with ED symptomatology and individuals with EDs tend to overestimate their body size compared to control individuals, some evidence suggests that body image distortions are not specific to this population, implying that they can underestimate their body size [24] or even be as accurate as individuals without ED symptomatology [32].

**Hypotheses 2 (H2)**: Participants with subthreshold ED symptomatology will show stronger auditory-driven body illusions, compared to control individuals.

H2 is based on the traditional hypothesis in support of a stronger influence of external sensory signals, leading to stronger body illusions in people with and subthreshold EDs [15–17].

**Hypotheses 3 (H3)**: Participants with subthreshold ED symptomatology, as compared to without ED symptomatology, will present unusual patterns of results in the finger elongation or shrinking waist illusion, suggesting impairments in the integration of artificial auditory signals into their body image.

H3 hypothesizes that participants with subthreshold ED symptomatology, as compared to people without ED symptomatology, will present unusual patterns of results, that is, the perceived finger elongation or shrinking waist will not necessarily occur in the ascending pitch condition (or not only in that condition, as in [24]. The results will shed light on whether the alteration in the mechanisms integrating auditory signals into body image is present only to natural signals related to body weight/size (e.g., footsteps) or it is linked to any auditory signals.

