S-EDE-Q†	To assess body EDs psychopathology. Self-administered questionnaire composed of 28 items using 7-point Likert scales ranging from 0 (not at all) to 6 points (markedly) about the previous 28 days. Four subscales are measured, including: dietary restraint (5 items), shape concerns (8 items), weight concerns (5 items), and eating concerns (5 items). For each subscale, the score ranges from 0 and 6 points. Participants will be grouped according to a global index score which is the average of the four subscale scores. As in Mond et al. [36], we will use a cut-off point ≥ 2.8 as clinically significant. Higher scores indicating a higher ED pathology. The S-EDE-Q have shown adequate internal consistency (Cronbach’s alpha ≥ .81 for all subscales), acceptable sensitivity (≥ 0.95), specificity (≥ 0.90), and positive (≥ 0.59) and negative (≥ 0.99) predictive values, and positive and significant correlation (≥ 0.70) with EDE diagnoses	X		
HSPS‡	To assess the tendency to process stimuli and information more strongly and deeply than others (sensory-processing sensitivity). Self-administered questionnaire composed of 27 items using 7-point Likert scales ranging from 0 (not at all) to 6 points (markedly). Five subscales are measured including: (1) sensitivity to overstimulation (9 items); (2) aesthetic sensitivity (6 items); (3) low sensory threshold (5 items); (4) fine psychological discrimination (4 items); (5) harm avoidance (3 items). For each subscale, the score ranges from 27 to 189 points. Higher scores indicate higher sensitivity level. A total global score will be obtained by averaging the five subscales. The HSPS have shown adequate internal consistency (Cronbach’s alpha ≥ 0.81 for all subscales) and construct validity in the adult Spanish population	X		

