MAIA§	To measure interoceptive body awareness. Self-administered questionnaire composed of 32 items using 6-point Likert scales ranging from 0 (never) to 5 points (always). Eight subscales are measured, including: (1) noticing (3 items); (2) not-distracting (2 items); (3) not-worrying (2 items); (4) attention regulation (7 items); (5) emotional awareness (5 items); (6) self-regulation (4 items); (7) body listening (3 items) (8) trusting (3 items). It generates a total direct score that ranges from 0 to 160 points. Higher scores indicate higher interoceptive awareness. A total global score will be obtained by averaging the six subscales. The MAIA have shown adequate internal consistency (Cronbach’s alpha 0.64 to 0.83 for all subscales)	X		
Auditory trials	Presented in four conditions: an anchor task (20 trials); a practice task (3 trials); an experimental block (30 trials) and a questionnaire block (3 trials)		X	X
Estimation of body position (finger/waist)	To assess estimation of location or position of fingertip/knuckle (allowing to calculate the estimated finger length can be calculated) and waist width after each auditory experimental trial		X	
Confidence task	It has been found that the reliability of perception might be linked to subjective rather than objective accuracy [41]. For example, previous studies using body illusions report that confidence was not accompanied by increases in objective accuracy (i.e., [42, 43]). Therefore, to assess the reliability of their estimations, after each auditory experimental trial, the feeling of confidence with the estimation of body part position will be explicitly assessed by asking the participants: “From one to seven, how confident are you of your estimation?” (7-point Likert scale)		X	X
Body feelings questionnaire (finger/waist) [25]	To assess subjective feelings about their finger/waist after the trials (susceptibility to the illusion). Participants will respond to a questionnaire containing 7-point Likert-type response items ranging from 1 (strongly disagree) to 7 (strongly agree) (Finger: 14 items; Waist: 13 items). In addition, a range of figures representing finger/waist will be presented. Each figure shows a whole hand/trunk selectively shrunk or elongated. Participants will be asked to choose one of the figures to describe the subjective feeling of the size of their finger/waist when listening to the sound. [see Additional file 2 and 3 for more details]		X	X

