Body visualizer task [44]	To assess the ability to accurately estimate body size (body size discrepancy) as well as the effects of sound feedback on perceived body size. Participants will adjust the weight related dimension of the body of a 3D avatar displayed on the screen to correspond to their perceived body size. Accuracy will be calculated according to the formula (estimated/actual body size) × 100 also-called body perception index (BPI) [45]. Specifically, a negative value represents an underestimation, whereas a positive value represents an overestimation	X		X

Body weight will be measured to the nearest 0.1 kg/% by means of a calibrated digital body fat scale (Sinocare CW 286). The Body feelings questionnaire will be directly built into Google Form and completed on a 10.1″ Android tablet (Lenovo M10)

^†^Spanish Version of the Eating Disorder Examination Questionnaire [46]

^‡^Spanish version of the Highly Sensitive Person Scale [47]

^§^The Multidimensional Assessment of Interoceptive Awareness [48]

Inclusion criteria will be: (a) normal (or corrected) auditory acuity; (b) sex: females (sex assigned at birth); (c) females within the healthy range of BMI (between 18.5 and 24.9) in order to reduce the likelihood of medical comorbidities that could affect the results (according to the World Health Organization index (WHO) [49]). Nevertheless, we recognize that weight/body mass index is not the sole predictor of potential co-occurring medical conditions. By doing so, we also avoid a potential confounding variable reported by [24]. This is in line with the criteria of healthy participants usually used in the field of eating disorders and body illusions research (e.g., [16]). Exclusion criteria: (a) lifetime history or presence of any significant brain injury, neurological condition, auditory pathology; (b) lifetime history or presence of a mental illness measured by self-report measures and screening questions; (c) lifetime history of underweight or overweight; (d) current use of psychotropic drugs (e.g. antidepressants) or intake of recreational synthetic or natural drugs; (e) inability to understand Spanish; (f) inability to provide consent; (g) out of age range; (h) pregnant status.

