#### Body visualizer task

The degree of body size discrepancy will be hand-coded by the experimenter into a data sheet. Per participant, a total of four summary estimations will be calculated [(baseline body size discrepancy) + (post-experiment body size discrepancy × 3 feedback conditions: ‘ascendent’, ‘constant’, ‘descendent’)] according to the BPI index (see Table 1 for more details).

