### Statistical analyses

#### Primary aim: auditory-driven changes in body perception Baseline measures

To determine differences between the groups, analyses will be performed with a Student's t-test paired comparison (for normal distribution) or Wilcoxon tests (for non-normal distribution) for ED symptomatology (EDE-Q), interoceptive body awareness (MAIA), sensory-processing sensitivity (HSPS) and body size discrepancy (Body visualizer tool).

#### Experiment 1 and Experiment 2

For the estimations of body part position/size, confidence task and items from the body feelings questionnaires we will follow a 2 × 3 ANOVA within-between interaction repeated-measures design (see Table 2). Specifically, we will use non-parametric ANOVAs on aligned rank (ART) data, suitable for ordinal data, using the R package ARTool [56]. The ANOVAs will involve a group factor with 2 levels (subthreshold EDs and controls) and a feedback condition factor with 3 levels (‘ascendent’, ‘constant’, ‘descendent’). Prior the analysis, assumptions of independence, normality and sphericity will be checked. As in [24], we will include the degree of body size discrepancy as covariate in case of significant baseline differences. Appropriate post-hoc tests will be conducted in case of significant differences.

**Table 2 Tab2:** ANOVA 2 × 3 design

Group	Feedback condition		
	Ascendent	Constant	Descendent
Subthreshold EDs	Subthreshold EDs–Ascendent	Subthreshold EDs–Constant	Subthreshold EDs–Descendent
Controls	Controls–Ascendent	Controls–Constant	Controls–Descendent

For body size discrepancy, we will follow a 2 × 3 ANOVA within-between interaction repeated-measures design (see Table 3). The ANOVAs will involve a group factor with 2 levels (subthreshold EDs and controls), a time factor with two levels (baseline and post-experiment) and a feedback condition factor with 3 levels (‘ascendent’, ‘constant’, ‘descendent’).

**Table 3 Tab3:** ANOVA 2 × 2 × 3 design

Group	Baseline	Experiment		
		Feedback condition		
		Ascendent	Constant	Descendent
Subthreshold EDs	Subthreshold EDs Baseline	Subthreshold EDs Post-experiment Ascendent	Subthreshold EDs Post-experiment Constant	Subthreshold EDs Post-experiment Descendent
Controls	Controls Baseline	Controls Post-experiment Ascendent	Controls Post-experiment Constant	Controls Post-experiment Descendent

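### Table 1's scoring rules for the body perception index, the MAIA and the HSPS contradict themselves; the MAIA conflict can change an analysed score, while the other two affect interpretation and stated range.

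*Protocol article*

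**What the plan says.** All three rules stand in Table 1 of the protocol article (section Participants).

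- **Body visualizer task.** "Accuracy will be calculated according to the formula (estimated/actual body size) × 100 also-called body perception index (BPI"). The row then adds that "a negative value represents an underestimation, whereas a positive value represents an overestimation". The data management section scores one baseline and three post-experiment estimates per participant "according to the BPI index (see Table 1 for more details"). The statistical analyses section compares the measure between groups at baseline, uses it as an ANOVA outcome, and may use it as an adjuster: "we will include the degree of body size discrepancy as covariate in case of significant baseline differences".
- **MAIA.** The row describes 32 items scored 0 to 5 and a direct total of 0 to 160. It names eight subscales of 3, 2, 2, 7, 5, 4, 3 and 3 items. It then says: "A total global score will be obtained by averaging the six subscales".
- **HSPS.** The row describes 27 items scored 0 to 6, in five subscales of 9, 6, 5, 4 and 3 items, and a global score that averages the five. It also says: "For each subscale, the score ranges from 27 to 189 points".

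MAIA and HSPS are compared between groups at baseline. They are also the outcomes named in H5 and H6 and in the secondary regressions.

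**The concern.** These are the rules by which an analyst would compute and read the scores, and each conflicts with another statement in its own row.

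For the BPI, the direction of distortion is at stake. The rationale for H1 allows for overestimation, for accuracy, and for participants who underestimate ("implying that they can underestimate their body size"). A sign rule that the formula can never satisfy leaves the reader without a correct statement of which values mean which.

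For the MAIA, the score itself is at stake: two analysts following the row could compute different global scores. The plan also admits outcomes to the regression only if their bivariate correlation is significant, so the choice of score could decide whether the MAIA is modelled at all.

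For the HSPS, the response coding and the level to which the range belongs are unclear, so neither the scores nor their plausibility limits can be checked against the table.

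**Working it through.** All inputs come from Table 1. The 75%, 90% and 125% estimates are illustrations.

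**BPI.** Formula: BPI = (estimated / actual) × 100.

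| Estimate as share of actual size | BPI as written | BPI − 100 |
|---|---|---|
| 75% | 75 | −25 |
| 90% | 90 | −10 |
| 100% | 100 | 0 |
| 125% | 125 | +25 |

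Both sizes are positive, so BPI > 0 always. A participant who underestimates by 25% scores +75, which the stated rule calls an overestimation. The described signs fit the last column, not the formula. Moving from one column to the other subtracts 100 from every value. Group differences, ranks, ANOVA effects and covariate slopes therefore stay the same.

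**MAIA.**
- Stated total: 32 × 5 = 160, so the 0 to 160 range is reproduced from the stated 32 items.
- Listed items: 3 + 2 + 2 + 7 + 5 + 4 + 3 + 3 = 29, and 29 × 5 = 145. Three items are unaccounted for.
- Subscales listed: 8. Subscales averaged: 6, unnamed. Six of eight can be chosen in (8 × 7) / 2 = 28 ways.
- Unlike the BPI shift, leaving subscales in or out does not move everyone by the same amount, so correlations and regression slopes can change.

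**HSPS.** Items: 9 + 6 + 5 + 4 + 3 = 27, which agrees with the stated 27.

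| Coding | Subscale sums | 27-item total | Mean of five sums |
|---|---|---|---|
| 0–6 (stated) | 0–54, 0–36, 0–30, 0–24, 0–18 | 0–162 | 0–32.4 |
| 1–7 | 9–63, 6–42, 5–35, 4–28, 3–21 | 27–189 | 5.4–37.8 |

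The stated 27 to 189 is reproduced in one cell only: the full total at 1 to 7 coding (27 × 1 and 27 × 7). No subscale reaches 189 under either coding. Changing the coding adds 1 to every item, so a mean of five sums rises by 27 / 5 = 5.4 for everyone, and no planned test changes.

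One HSPS question can matter: sums or item means. With sums, the mean of five subscales is total / 5 and every item counts equally. With item means, an item in a subscale of k items has weight 1/(5k): 1/45 in the 9-item subscale and 1/15 in the 3-item subscale, a ratio of 3. The row does not say which applies. The S-EDE-Q row, by contrast, gives each subscale a 0 to 6 range, which implies item means there.

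**The case against.** The strongest reply is that most of this is table wording. No planned analysis counts or classifies over- and underestimators; the BPI enters as a continuous score, and the intended centred reading is easy to guess. The HSPS averaging rule can be carried out, and its wrong range changes no result. The six in the MAIA row may be a slip for eight, and 0 to 160 agrees with the stated 32 items. The study is also openly exploratory. Most of this stands, and it limits the point to what the verdict states. It does not remove the need for a correction, since an exploratory score must still be computable in one way and read in the right direction.

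Four stronger readings are tempting, and the documents do not support them.

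- **That H1 needs an absolute index, |BPI − 100|, because over- and underestimation cancel in a signed mean.** H1's rationale is directional, and the article uses the phrase degree of body size discrepancy for the planned index itself. An absolute value would be an added estimand. No section expressly names the BPI as the H1 outcome, although that is a reasonable inference.
- **That two MAIA subscales are dropped.** The row never says so; this is one reading of a conflict.
- **That averaging the five HSPS subscales weights items unequally.** This holds only for item means, which the row does not specify.
- **That MAIA and HSPS are the only secondary outcomes.** The regression text offers them as examples, and a secondary correlation with EDE-Q scores is also planned.

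**Conclusion.** The contradictions are real and follow from Table 1 alone, but they differ in weight.

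- **MAIA:** the only conflict that clearly can alter an analysed score. The global score has no unique definition (six unnamed against eight listed), and the item counts fall short by 3 (145 against 160 points). How far results would move cannot be worked out from the documents, since it depends on the data and on the subscales used.
- **BPI:** an error of interpretation. Read literally, the rule makes all participants overestimators. The planned group tests are the same with or without centring.
- **HSPS:** an error of range and coding. The coding difference is a constant shift; the sum-or-mean question could change item weights, but only if means are used.

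The assumptions are that body sizes are positive and that subscale ranges refer to sums of the listed items. A reader might infer that the primary-aim tests are invalid. They are not affected by these scoring contradictions.

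**What to change.** Correct Table 1 before any scores are computed.

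1. **BPI:** define body size discrepancy as BPI − 100, so that negative means under- and positive means overestimation. Alternatively keep the ratio and state that values below or above 100 carry those meanings. |BPI − 100| may be added as a supplementary measure, labelled as such.
2. **MAIA:** fix one global score, either the mean of all eight subscales or the mean of six that are named. Reconcile the subscale item counts and the 0 to 160 total with it.
3. **HSPS:** state the response coding actually used, attach the matching range to the 27-item total (0–162 at 0 to 6 coding, 27–189 at 1 to 7), and say whether subscales are sums or item means.

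The cost is a table correction. It needs no new data and no change to the planned models.

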## Participants

The experiment will be conducted individually in a quiet laboratory room [see Additional file 1, section A]. In keeping with previous literature and to facilitate the comparison and interpretation of the results because of the variability shown in related measures, the sample will comprise young adult females (sex assigned at birth) in the 18–24 age range, where the prevalence of EDs in this population is the highest [34]. However, it should be pointed out that previous evidence has reported high prevalence of EDs not only in female samples but also in other populations such as in men or gender diverse individuals [35–37]. Additionally, we decided to focus on the waist because this body part has been shown to be particularly emotionally salient for females and a reliable indicator of body mass index (BMI) [4, 38]. Participants will be recruited through public advertisements and social media posts (convenience sampling) and they will be paid or compensated with grade points for their time. To split the sample into participants with and without ED symptomatology, the Spanish Eating Disorder Examination Questionnaire (S-EDE-Q) [39]) will be administered (see Table 1 for more details). The pre-screening will allow to form two groups of similar size: once the desired participant sample size has been reached for one of the groups, only participants falling into the other group defined for the study will be invited to take part. The S-EDE-Q have demonstrated good psychometric properties in young female adults in Spain [39]. A global EDE-Q score ≥ 2.8 has been shown to provide an optimal trade-off between sensitivity and specificity when it is used for screening in primary care [40]. Available resources for participants will include psychoeducation and support for body image and eating-related concerns, provided by a team member. The availability of these resources will be specified in the informed consent. Moreover, to not assume that all individuals are cis-gender, gender identity will be assessed through an additional question.

**Table 1 Tab1:** Overview of study measures and data collection timepoints

Measure	Description	Baseline	Experiment	
			1	2
Demographic data	Participants’ age. In addition, BMI will be calculated with the following formula: BMI = weight (kg)/(height (m)^2^) following the World Health Organization’s criterion [45]	X		
Information consent	Written informed consent	X		

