### General experimental procedure

Table 1 shows an overview of study measures and data collection time points and Fig. 3 shows a schematic representation of the experimental procedure. After reading the information sheet and signing the information consent, participants will complete the S-EDE-Q. Participants eligible to take part will be invited to the lab at Loyola Andalucia University. The experimental procedures will be implemented, and all data will be collected, by a postgraduate Ph.D. researcher trained by senior members of the research team. After reading the information sheet and signing the information consent, demographic data (age and BMI) will be collected. Later, participants will complete two questionnaires related to the secondary aim (see Table 2). The Multidimensional Assessment of Interoceptive Awareness Scale (MAIA) (to assess interoceptive body awareness) and the Highly Sensitive Person Scale (HSPS) (to assess sensory-processing sensitivity). The same participants will complete both Experiments 1 and 2.

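### Limiting entry to BMI 18.5–24.9 reduces BMI confounding but does not avoid it; raw waist width and the whole-sample analyses stay exposed, and measured BMI is in no listed comparison or model

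*Protocol article*

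**What the plan says.** In the Participants section, inclusion criterion (c) admits "females within the healthy range of BMI (between 18.5 and 24.9" and exclusion criterion "c) lifetime history of underweight or overweight" narrows the weight range further. After the inclusion criterion the text adds: "By doing so, we also avoid a potential confounding variable reported by [24". The cited study is not available here; from the context the confounder is weight or BMI.

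The two groups are defined by the EDE-Q cut-off of 2.8, and the only balancing described is on numbers: "The pre-screening will allow to form two groups of similar size". The same section calls the waist "a reliable indicator of body mass index (BMI".

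Under General experimental procedure, "demographic data (age and BMI) will be collected". The baseline group tests in Statistical analyses are listed as "for ED symptomatology (EDE-Q), interoceptive body awareness (MAIA), sensory-processing sensitivity (HSPS) and body size discrepancy (Body visualizer tool"; BMI is not among them. The one covariate named for the ANOVAs is baseline body size discrepancy, entered only if it differs significantly. The secondary regressions name only body position and size measures as inputs.

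The two body-size outcomes are on different scales. The Body Visualizer score in Table 1 divides estimated by actual size. Perceived waist width, under Data management, is the mean of the opening and closing responses. No division by the participant's measured waist width is stated, although that width is taken before Experiment 2.

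**The concern.** Restriction and balance are different things. Two groups can both lie inside 18.5 to 24.9 and still have different mean BMI. Nobody is randomised to symptom level, and two of the four EDE-Q subscales that form the grouping score are shape concerns and weight concerns, so a link between group and body size within the normal range is plausible. The protocol does not show that one exists.

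The article says that the problem has been avoided, and then neither examines nor adjusts for the variable it has measured. If the subthreshold group is somewhat heavier or lighter on average, part of a group difference in raw waist width would reflect actual body size and could be reported as a perceptual effect of ED symptoms. The same path runs through the correlations of waist estimates with EDE-Q and the regressions of MAIA and HSPS on them. The study is meant to seed a confirmatory trial, so a confounded pattern would be carried forward.

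**Working it through.** The protocol gives no BMI figure by group and no sample size calculation, so there is no stated figure to reproduce. The check asks how much BMI difference restriction can leave, and which results it can reach.

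**Inputs from the protocol:** BMI range 18.5 to 24.9 (width 6.4); 50 per group; waist width as a raw average; body perception index = estimated/actual × 100; feedback condition within-subject with 3 levels.

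**Assumptions (none given in the protocol):** before restriction, BMI is normal with mean 21.5 in controls and 22.5 to 24.5 in the subthreshold group, SD 2.5 to 3.5; within-group correlation r between BMI and the outcome of 0.2 to 0.6; two-sided 5% test.

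**Step 1: what restriction leaves.** The mean of a truncated normal is μ + σ[φ(a) − φ(b)]/[Φ(b) − Φ(a)], with a = (18.5 − μ)/σ and b = (24.9 − μ)/σ. For SD 3.0 and means 21.5 and 23.5, the within-range means are 21.64 and 22.27, a difference of 0.64 before rounding. The remaining difference in kg/m² (standardised difference in brackets) is:

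| SD | 1 unit apart before | 2 units | 3 units |
|---|---|---|---|
| 2.5 | 0.43 (0.26) | 0.85 (0.53) | 1.22 (0.78) |
| 3.0 | 0.32 (0.19) | 0.64 (0.38) | 0.93 (0.56) |
| 3.5 | 0.25 (0.14) | 0.49 (0.28) | 0.73 (0.43) |

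Restriction removes more than half of the raw difference in every case, but never all of it.

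**Step 2: effect on a group main effect.** With no true group effect, spurious d = d_BMI × r. The test has 98 degrees of freedom and noncentrality d × √(50/2) = 5d. For d_BMI 0.4 and r 0.6, d = 0.24, the noncentrality is 1.2 and the rejection rate is 22.1%. Rejection rates under the null:

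| d_BMI | r = 0.2 | r = 0.4 | r = 0.6 |
|---|---|---|---|
| 0.2 | 5.5% | 6.8% | 9.1% |
| 0.4 | 6.8% | 12.4% | 22.1% |
| 0.6 | 9.1% | 22.1% | 43.0% |

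**Step 3: effect on the group-by-feedback interaction.** If BMI adds the same amount β × BMI to each of a woman's three condition means, it drops out of any difference between conditions. In 4,000 simulated studies per setting with r = 0.6, the main effect was rejected in 8.7%, 21.6% and 41.4% of runs for d_BMI 0.2, 0.4 and 0.6. The ascending-minus-constant contrast between groups was rejected in 5.4%, 5.25% and 5.2%. The cancellation fails if BMI changes susceptibility to the sound, or if the shift in centimetres is proportional to width. In the second case the shift is k × W, and its difference between conditions still contains W.

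**Step 4: whole-sample analyses.** The listed summary scores are condition averages, and the plan does not say that differences between conditions will be entered instead. If BMI is the only link, the induced correlation equals r(BMI, questionnaire score) × r(BMI, waist estimate). Nothing in the analysis cancels it. The closing trials also start at 2.0 times the participant's own waist width, so the task itself scales with body size.

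**The case against.** Restriction is a recognised way to control confounding, and the lifetime under- and overweight exclusion tightens it. Feedback is within-subject, so the illusion hypotheses rest on an interaction from which an additive BMI effect cancels. The body perception index is already a ratio. The hypotheses are declared exploratory, and an article may leave covariates and baseline tables to a fuller plan. BMI may also be partly a consequence of symptoms such as dietary restraint, so routine adjustment is not clearly right.

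Much of this stands. A reader might infer that H2–H4 as a whole are confounded by BMI. The documents do not support that: the relevant contrast is within-person, and they offer no evidence that BMI alters susceptibility to the tones. Nor do they tie finger outcomes to BMI.

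A reader might also point to expected chance imbalance. With BMI uniform over the range, SD = 6.4/√12 = 1.85, SE = 1.85 × √(2/50) = 0.37, and 1.96 × 0.37 gives 0.73 units. That is ordinary sampling variation, already reflected in the test's standard error; it is not evidence of confounding.

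The deferral argument does not stand. The article asserts that the confounder is avoided and then lists its baseline tests and its sole covariate, neither of which includes BMI. Conditional adjustment for body size discrepancy is no substitute, because that variable measures accuracy of estimation, not size.

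**Conclusion.** The claim of avoidance is stronger than the design delivers; restriction reduces BMI confounding. The results left open are the group main effect on waist width and the whole-sample correlations and regressions of waist estimates with EDE-Q, MAIA and HSPS. H1 is partly protected through the ratio index, though percentage misestimation could still vary with body size. The interaction behind H2–H4 is protected unless BMI changes susceptibility or centimetre shifts scale with body size.

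The 5.5% to 43% range applies to an exposed group main effect only. It rests entirely on assumed BMI differences and correlations, and on BMI differing systematically between groups, which the protocol neither shows nor rules out. That the cited study's confounder is BMI is read from context. The point is worth correcting before analysis because the correction uses data already collected; it does not undermine the central interaction tests.

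**What to change.** - In inclusion criterion (c), say that the restriction reduces the potential confounder.
- Report BMI and age by group.
- Express waist estimates relative to the measured waist width, or adjust for that width.
- Pre-specify BMI as a continuous covariate, at least as a sensitivity analysis, in the between-group comparisons of body size discrepancy and waist width and in the whole-sample correlations and regressions. Do this whether or not baseline BMI differs significantly.
- Show unadjusted and adjusted results together, with a note that BMI may lie partly downstream of symptoms.

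The cost is one degree of freedom and a model that takes a continuous covariate alongside the aligned-rank ANOVA, for example a linear mixed model. The plan's own conditional covariate, body size discrepancy, already raises that need. No new data are required. Matching controls on BMI at screening is optional.
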